### Interim analyses {21b}

Not applicable. This clinical study does not plan to conduct an interim analysis.

### Methods for additional analyses (e.g. subgroup analyses) {20b}

The uniformity of the treatment effect for the primary efficacy outcome will be examined for the following subgroups using all analysis sets.Age group (<54, ≧54 years)Sex (Male, female)Race (Korean, non-Korean) (Note that this variable will not be analysed if the numbers of non-Korean are low)ALS type (Bulbar, limb)

The homogeneity of the treatment effect across subgroups will be investigated using analytical methods. Statistical tests for the presence of a treatment-by-subgroup interaction will be performed by including the interaction term in the primary analysis model. If the treatment-by-subgroup interaction is found to be statistically significant at the 10% level, this will be taken as evidence of heterogeneity of the treatment effect across subgroups.

### Methods in analysis to handle protocol non-adherence and any statistical methods to handle missing data {20c}

Data will be analysed using the intention-to-treat (ITT) set. This set will be applied to all randomized subjects. Subjects will be randomized and analysed for efficacy evaluation.

For the primary and secondary efficacy endpoints, multiple imputation (MI) methods will be used to handle the missing values, if applicable. The multiple imputation method replaces each missing value with a set of plausible values that represent uncertainty and imputation with the right value. The method for imputing variables is available in SAS PROC MI for both monotone and arbitrary missing data patterns and will be implemented with the PREDICT MEAN MATCHING option. In addition, sensitivity analyses will be conducted for the primary efficacy endpoint to examine the impact of missing data using the SAS PROC MI for both monotone and arbitrary missing data patterns using the REGRESSION option.

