Based on the CAFS data obtained in phase I/II clinical trials, the number of subjects was calculated for two hypotheses to demonstrate the study group's superiority to the control group at 6 and 12 months. Table 3 shows the estimated sample size of this clinical study. For Hypothesis 1, the calculated number of subjects in study Group 1 is 19, and the calculated number of subjects in the control group is 19. For Hypothesis 2, the calculated number of subjects in study Group 2 is 32, and the estimated number of participants in the control group is 32. Since a single control group was used for both study Group 1 and study Group 2 in this clinical study, a larger number of subjects (32) in the control group for two hypotheses was selected. In conclusion, the minimum number of subjects required for this clinical study was 19 for study Group 1, 32 for study Group 2, and 32 for the control group. Considering the 15% (around) dropout rate, the number of subjects was increased to 23 for study Group 1, 38 for study Group 2, and 38 for the control group. However, to satisfy the stratified block randomization, a randomization ratio was generated at 1:2:2 for each group. Therefore, to satisfy the ratio of 1:2:2, 23 subjects in study Group 1, 46 subjects in study Group 2, and 46 subjects in the control group will be enrolled (115 subjects in total).

**Table 3 Tab3:** Estimated sample size considering dropout rate

	Study Group 1	Study Group 2	Control group	Total No. of subjects
Cases for efficacy evaluation	19	32	32	83
Cases including dropouts (approximately 15%)	23	46	46	115

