## Statistical methods

### Statistical methods for primary and secondary outcomes {20a}

All inferential statistical analyses will be based on a two-sided test with a type I error rate of 0.05.

The two primary efficacy endpoints for this study are as follows:Joint rank test using CAFS between study Group 2 and the control group at 12 monthsJoint rank test using CAFS between study Group 1 and the control group at 6 months

To protect the type I error rate for testing the two hypotheses, a hierarchical test procedure will be used. The hypotheses will be tested in the following order:

1.

H_0_: No difference between study Group 2 and the control group at 12 months.

H_1_: There is a difference between study Group 2 and the control group at 12 months.

2.

H_0_: No difference between study Group 1 and the control group at 6 months

H_1_: There is a difference between study Group 1 and the control group at 6 months.

If the first null hypothesis is rejected at an alpha level of 0.05, then study success is claimed. Next, the second null hypothesis is tested at an alpha level of 0.05. If the first null hypothesis is not rejected at an alpha level of 0.05, then the study fails.

At individual points, the differences between the study and control groups will be evaluated by analysis of covariance (ANCOVA) with covariate adjustment of baseline ALSFRS-R score, ALSFRS-R score progression rate, and stratification factors. When a 95% two-sided confidence interval for differences in mean joint rank scores between the study and control groups at each point does not comprise 0, it is considered that the study group's results are superior to those of the control group.

Additionally, for the primary efficacy endpoints, a generalized Gehan-Wilcoxon rank test will be used to compare CAFS between study groups and control groups as a supportive analysis.

The secondary efficacy endpoints for this study are as follows:Joint rank test using CAFS between study Group 2 and the control group at 6 monthsChange in ALSFRS-R score from baseline between study Group 2 and the control group at 12 monthsChange in ALSFRS-R score from baseline between study Group 1 and the control group at 6 monthsComparison of the time to an event at 6 months between study Group 1 and the control groupComparison of the time-to-event at 12 months between study Group 2 and the control group

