Although the sample size was calculated considering the usual dropout rate in clinical trials, the ALSUMMIT trial protocol was designed to require a long-term follow-up time of up to 12 months. In the previous phase II clinical trial, the primary outcome was determined 6 months after the first treatment. Therefore, a higher dropout rate may be developed in the ALSUMMIT trial. Multiple imputations will estimate the missing value, but if the dropout rate is higher than the initial expectation and appropriate data analysis is difficult with high dropout rate, additional recruitment of new participants or addition of a new treatment arm could be considered after the discussion with FDA and MFDS.

We hope that data from the ALSUMMIT trial would contribute to developing the BM-MSC therapeutic strategy for ALS.

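### The one missing-data sensitivity analysis the article names keeps the missing-at-random assumption of the main analysis, so it cannot show whether informative dropout affects the primary result

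*Protocol article*

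**What the plan says.** All of this is in the protocol article.

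- **Missing data {20c}.** The analysis covers all randomized participants. "For the primary and secondary efficacy endpoints, multiple imputation (MI) methods will be used to handle the missing values, if applicable". The main imputation "will be implemented with the PREDICT MEAN MATCHING option". The article then says that "sensitivity analyses will be conducted for the primary efficacy endpoint to examine the impact of missing data using the SAS PROC MI", and completes the sentence with the method: "for both monotone and arbitrary missing data patterns using the REGRESSION option". No shift, reference-based or tipping-point element is mentioned.
- **Statistical methods {20a}.** The other additional analysis of the primary endpoint changes the test: "a generalized Gehan-Wilcoxon rank test will be used to compare CAFS between study groups and control groups as a supportive analysis". It is not described as changing the missing-data assumption. In the testing order, Group 2 against control at 12 months comes first, and the study fails if that null hypothesis is not rejected.
- **Sample size {14}.** "Considering the 15% (around) dropout rate, the number of subjects was increased to 23 for study Group 1". The other two arms went from 32 to 38, and then to 46 to fit the 1:2:2 ratio.
- **Discussion.** Because follow-up is longer than in the phase II trial, "a higher dropout rate may be developed in the ALSUMMIT trial". Multiple imputation is named as the means of filling the missing values, with further recruitment or a new arm as a possibility if dropout makes the analysis difficult.

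**The concern.** A sensitivity analysis for missing data should vary the assumption that the data cannot check. Here that assumption is that a participant who leaves would have continued like observed participants with the same recorded history. Predictive mean matching and regression both fit a model to the observed values and draw the missing ones from it. The first borrows an observed value from a near match; the second draws from a fitted normal distribution. Changing from one to the other probes normality and linearity and leaves the missing-at-random assumption as it was.

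The two results will therefore tend to agree whether or not dropout is informative, and the agreement is likely to be reported as robustness to missing data. The comparison most exposed is Group 2 against control at 12 months, which has the longer follow-up and alone decides study success.

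**Working it through.** **1. Inputs from the article, reproduced.** The printed sample-size formula is N = (z_α + z_β)² / [12c(1−c)(p−½)²], with two-sided α = 0.05, power 0.80 and c = 0.5.

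- 6 months, p = 0.769: N = 36.16, so 19 per arm, as stated.
- 12 months, p = 0.705: N = 62.26, so 32 per arm, as stated.
- Dropout of 15%: 19/0.85 gives 23 and 32/0.85 gives 38, as stated. The total is 23 + 46 + 46 = 115.

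The sample size is not in dispute. It supplies two reference points for the 12-month comparison:

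- 15% of 46 is 6.9, or about 7 participants per arm. A loss of 14 per arm, (46 − 32)/46 = 30%, brings the comparison down to its 32 evaluable per arm.
- With equal arms of n, the difference in mean ranks is n(2p − 1). The planned effect is 46 × (2 × 0.705 − 1) = 18.9 ranks among 92 participants.

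**2. What the two methods can see.** On the ALSFRS-R scale, suppose a share π of the active arm is missing and those participants truly lose δ points more than missing at random predicts. Any missing-at-random imputation then overstates the active-arm mean by about π × δ.

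A simulation of 46 against 46 (400 trials per setting, 10 imputations) behaves this way. Values are mean treatment differences in ALSFRS-R points:

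| π, δ | π × δ | Complete data | PMM (excess) | Regression (excess) |
|---|---|---|---|---|
| 15%, 3 | 0.45 | 2.64 | 3.06 (0.42) | 3.10 (0.46) |
| 15%, 6 | 0.90 | 2.05 | 2.89 (0.84) | 2.94 (0.89) |
| 30%, 3 | 0.90 | 2.05 | 2.88 (0.83) | 3.01 (0.96) |

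**3. The same on the joint-rank scale.** A second simulation ranked 46 against 46 and analysed the ranks by ANCOVA on baseline score and progression rate (600 trials per setting, 10 imputations). It had no deaths and no treatment effect other than the planted one: active-arm dropouts declined 5 or 10 points more than comparable completers. Values are mean rank differences, with simulation standard errors of about 0.2:

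| Dropout per arm, extra decline | Complete data | PMM | Regression | Delta set to the true shift |
|---|---|---|---|---|
| 15%, 0 | 0.24 | 0.25 | 0.25 | 0.21 |
| 15%, 5 | −2.81 | −0.01 | −0.02 | −2.85 |
| 15%, 10 | −4.99 | −0.01 | 0.06 | −4.88 |
| 30%, 5 | −5.82 | −0.01 | 0.00 | −5.62 |
| 30%, 10 | −10.03 | 0.05 | 0.05 | −9.72 |

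The mean difference between the two planned methods was at most 0.06 ranks. Within single trials the difference had a standard deviation of 0.8 to 1.2 ranks. They agreed on significance in 97.5% to 99.3% of trials. Both missed the whole planted disadvantage, 2.8 to 10.1 ranks.

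**4. How far the sizes can be read.** If the central eligibility rate of 1.03 points per month {10} continued for a year, decline would be 12 × 1.03 = 12.4 points. Extra losses of 5 and 10 points are 40% and 81% of that, so the larger one is extreme. The delta column recovers the truth because delta was set equal to it. In the 15%, 6-point setting of step 2, a delta of only 3 gave 2.49 against a truth of 2.05, which is still 0.44 too large. A single delta is therefore not enough.

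**The case against.** **Left to the analysis plan.** The article condenses a longer document, it says sensitivity analyses in the plural, and delta grids or reference-based imputation usually belong in an analysis plan. A reader might infer that the trial has no missing-not-at-random analysis. The article does not support that, because an unseen plan may contain one. What stands is narrower: the article states a purpose and a method for it, and that method does not serve the purpose.

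**The exposed group is limited.** Deaths enter the joint rank through the survival component {12}. Participants who stop treatment but remain in the study stay in follow-up {11b}. ALSFRS-R and events can be assessed remotely after study discontinuation {18b}. This is fair, and it confines the problem to living participants without a score at the endpoint visit. Remote assessment stops at withdrawal of consent, so the group is reduced but not removed.

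**Decline-driven dropout may be missing at random.** If participants leave because of decline already recorded, and earlier scores are in the imputation model, missing at random can hold. This also stands. Only decline beyond what the recorded history predicts escapes. The article does not say that participants leave because they are declining, and it lists no predictors for either imputation, so it cannot be said that the two models share them.

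**The sizes are planted.** They are. The article gives no post-dropout decline, the shift was applied to the active arm only, and deaths were not simulated.

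**Conclusion.** The point holds as a defect of a stated method. The named sensitivity analysis varies the form of the imputation model and leaves the missing-at-random assumption untouched, so it cannot examine the impact of informative dropout. That conclusion rests on how the two PROC MI options ordinarily work and does not depend on any simulated setting.

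The size of a possible bias does depend on assumptions. With 15% to 30% dropout and 5 to 10 points of extra decline in the active arm, it was 2.8 to 10.1 ranks, against a planned 18.9. These are illustrations: the settings are not the article's, apart from the 15%, and the planted cases were run with no other treatment effect.

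Three stronger readings are tempting and not supported:

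- That the trial will overstate its effect by some percentage. Bias could take either sign and may be absent.
- That the sponsor expects dropout above plan. The Discussion says it may occur.
- That the REGRESSION run is worthless. It remains a legitimate check of normality and linearity.

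**What to change.** Keep the REGRESSION run and describe it as a check of the imputation model's form. Before unblinding, add at least one of the following for both primary joint rank comparisons, with the 12-month Group 2 comparison as the priority:

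- **Delta-adjusted imputation.** Worsen the imputed ALSFRS-R values of active-arm participants before ranking, over a stated grid (for example 0 to 6 points), and report the tipping point at which the conclusion changes. Report the number of imputed values per arm beside it, so that readers can judge whether the tipping shift is plausible.
- **Control-based imputation.** Impute active-arm dropouts from the control-arm model, then rank and analyse as planned.

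State the imputation predictors, including earlier ALSFRS-R scores, for every run. If the full analysis plan already contains such analyses, the article's description should say so.

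The MNAR statement of PROC MI supports both, so the cost is a few lines of code and one paragraph in the analysis plan. Design, sample size and conduct do not change. The downside is a little more reporting and possibly a less favourable bound.

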### Plans to give access to the full protocol, participant-level data and statistical code {31c}

Not applicable. There are no plans for granting public access to the full protocol, participant-level dataset, or statistical code.

## Oversight and monitoring

### Composition of the coordinating centre and trial steering committee {5d}

The Clinical Research Organization (CRO) is designated for clinical operation (including periodic site monitoring), data management, safety reporting management, medical oversight, data analysis and medical writing; therefore, a weekly/biweekly meeting will be held during the clinical trial process with the key person of CRO, and a monthly/quarterly report on each item will be received. In this process, only blinded staff will participate, and unblinded items will not be included in all meetings and reports. If necessary, unblinded staff will hold meetings, and unblinded reports will be forwarded to only the unblinded project manager.

The trial steering committee has executive authority regarding the study. The trial steering committee is composed of the Chief Executive Officer (CEO), Chairman, and Chief Financial and Marketing Officer (CFO) of Corestem, who are not associated with the execution of the study. Steering committee meetings will be held every week, and the project leader will report the progress of the clinical trial to the committee. The trial steering committee will give the final decision for the necessary funding, finances, and recruitment for the study. It is the committee's role to assign IDMC members and to make a final decision upon receiving the recommendations from IDMC.

### Composition of the data monitoring committee, its role and reporting structure {21a}

The IDMC consists of 3 independent experts in the fields of neurology and biostatistics. IDMC members and their contact information are provided, and they shall have no substantive conflict of interest with the study. IDMC is primarily responsible for reviewing the safety data and evaluating the study progress. Additionally, IDMC provides recommendations to the sponsor concerning continuation, termination, or other modifications of the study based on the observed adverse effects of the treatment under investigation. The operation of IDMC shall comply with the predetermined IDMC Charter that sets forth the members, roles, responsibilities, and communication affairs. IDMC shall convene at least three rounds of meetings (after 28 randomized subjects complete the main study, after an additional 56 randomized subjects complete the main study, and after 14 randomized subjects complete the main study and the observational study) to review the benefit-risk data.

During the trial, IDMC will be responsible for periodically reviewing the study results, evaluating the treatment groups for excess adverse events, determining whether the basic study assumptions remain valid, assessing whether the overall integrity, scientific merit, and conduct of the study remain acceptable, and making recommendations to the sponsor.

### Adverse event reporting and harms {22}

Subjects are instructed to report any adverse events voluntarily, and investigators are responsible for identifying adverse events at regular or additional visits through interviews or medical examinations. Information on adverse events, such as occurrence date, disappearance date, severity, and consequence of the adverse event, actions were taken regarding investigational products, causal relationship with investigational products/concomitant medication, suspected cause other than investigational products and concomitant medication, treatment of the adverse event, and others will be collected and recorded. To identify acute adverse events after administration of investigational products, subjects will be monitored for blood pressure, pulse, body temperature, and respiration at approximately 6-hour intervals for at least 24 h after administration of investigational products. A serious adverse event must be reported to the sponsor within 24 h from the time of the event and acknowledged by the investigator. In addition, especially significant adverse events as defined below will be collected and reported to the sponsor immediately (within 24 h).

Suspected transmission from an infection source by the investigational product as defined below is also considered an especially significant adverse event.

Organisms, viruses, or infectious particles are considered infection sources regardless of pathogenicity. Transmission from an infection source is suspected if a subject exposed to drugs has clinical symptoms or obtains laboratory examination results that imply infection. The term especially significant adverse event is only used when investigational product contamination is suspected. Detailed reporting of serious adverse events is shown in Fig. 2.

**Fig. 2 Fig2:**
[figure not shown]
Safety management workflow. SIS, safety information system

### Frequency and plans for auditing trial conduct {23}

At least one audit is planned for all five sites to review the clinical study data, source document, and eCRF, which will be conducted by an independent agency delegated by the sponsor.

### Plans for communicating important protocol amendments to relevant parties (e.g. trial participants, ethics committees) {25}

When obtaining approval for a clinical trial or a change of approved clinical trial is needed, the related protocols and comparison table for change will be approved by the IRB and, if required, to the regulatory authorities. Unless a revision of the clinical trial protocol is desperately needed to eliminate the immediate risks posed on the subjects or is related to logistics or operations (such as changes in medical monitors and contact information), then a revision of the clinical trial protocol must be approved by both the IRB and the regulatory authorities. An informed consent form must be revised every time the clinical trial process is updated, or any new information that may affect the subject's decision to participate in this clinical trial becomes available. The IRB-approved final informed consent form shall be provided to the sponsor for submission to the regulatory authorities.

### Dissemination plans {31a}

Regardless of the results of this clinical trial, the sponsor will disclose the information of the clinical trial to medical practitioners and the general public through academic conferences or journals. The sponsor will comply with all requirements for the publication of clinical trial results. By signing this clinical trial protocol, the investigator agrees to use the results of this trial for the purposes of registration, presentation, and provision of information for medical/pharmaceutical experts. The sponsor shall have a right to review the clinical trial results to be declared to any journal in advance. Upon completion of clinical trial data analyses at all sites, the sponsor will keep the investigators notified of such results in the form of a report.

The sponsor shall have exclusive ownership of all data and results derived from and a right to publish the results of this clinical trial. In no case may the investigator publish, declare, present, or make public any part of the results of this clinical trial, unless otherwise agreed in writing by the sponsor. As such, the sponsor shall also ensure that the investigators do not publish, declare, present, or make public the results. To use only accurate and verified data, the investigator must provide all published drafts or presentation manuscripts prepared before publication or presentation to the sponsor for discussion, and the presentation must be withheld until written approval is received.

Regarding the clinical study results, the investigator agrees not to publish the results of their institution or some institutions before announcing the results collected from all clinical trial institutions. However, there are exceptions in cases where all institutions' clinical investigators and sponsor officially recognize the results.

